
### *Data collection*

#### *Quantitative component*

The quantitative component will have three sources of data: 1) participant self-report; 2) electronic medical records; and 3) passive data (e.g., on app use to assess fidelity). At T1, T2 (3 months) and T3 (6 months), a study questionnaire will be administered to participants online or, if needed, with a hardcopy, especially to assess implementation outcomes.

At T1, the questionnaire will also ask about socio-demographics (e.g., year of birth, preferred language, sex, sexual orientation, ethnic group identity, immigration, education, income) and digital technology use as well as pose general health questions for patients (year of diagnosis with HIV, treatment satisfaction) and clinical practice questions for physicians (years practicing in HIV, current number of HIV patients). The measures of digital technology use are as follows: frequency of mobile device use (adapted from Schnall et al., 2018), having a health app on one's mobile device (Mahmood et al., 2019), extent of health app use (adapted from Balapour et al., 2019), confidence in reporting medical information using mobile technology (Balapour et al., 2019), and intention to report personal health data with a mobile device app, if asked by a provider (Balapour et al., 2019). All of this information will help contextualize the findings and describe the sample (see the Appendix for the patient and physician questionnaires). Clinical data, namely, HIV viral load in copies/mL, to determine viral suppression, will be extracted from patients' medical health record at the clinic, at T1 and T3.

## Qualitative component

The qualitative component will have three sources of data: 1) 1-hour focus groups with all physicians (T2, T3); 2) 45-minute interviews with patients (T2, T3), until core theme saturation (an intermediate sample of 15 should be sufficient at each time point; Hennick et al., 2017); and 3) the Application Manager field notes, recorded on a standardized form (T1-T3). Focus groups and patient interviews will be conducted, if possible, through a teleconferencing platform such as Zoom. Participants will have the option of accessing the teleconference by telephone or the Internet. The patient's name will not be shown. Audio recordings of the focus groups and interviews will be manually transcribed, extracting nominal information. Each will be guided by a similar semi-structured interview schedule, in English or French, depending on preferred language. It will ask about the participants' experience with I-Score use and its implementation and about facilitating and impeding factors. The interview schedules can be found in the Appendix.

The schedule of study procedures for patients and physicians can be found in Table 1.

## Study metrics and instruments

Details on the constructs assessed; the instruments and metrics used; the chosen thresholds for success, if applicable; the participant group contributing data; and the timing of data collection are presented in Table 2. Many of the chosen metrics are based on those recommended by Stover et al. (2020). Importantly, the authors emphasize the need to standardize evaluation metrics in patient-reported measure implementation and to distinguish between those used to assess perceptions of the innovation and those used to assess the implementation strategy. Not meeting the set thresholds for success, in this study, will signify that modifications are necessary before proceeding to a definitive trial (Thabane et al., 2010).

Table 1. Schedule of study procedures for participants

| Procedure                                                  | Timeline               |                        |                        |                        |
|------------------------------------------------------------|------------------------|------------------------|------------------------|------------------------|
|                                                            | Prior to study start   | Study start (baseline) | Month 3                | Month 6                |
| Be screened and/or consent                                 | Patients
Physicians |                        |                        |                        |
| Attend educational meeting                                 | Physicians             |                        |                        |                        |
| Receive training on the I-Score measure and Opal           | Patients
Physicians | Patients
Physicians | Patients
Physicians | Patients
Physicians |
| Complete the I-Score measure via Opal                      |                        | Patients               | Patients               | Patients               |
| Examine the I-Score measure results via the ORMS dashboard |                        | Physicians             | Physicians             | Physicians             |
| Attend HIV patient-physician visit (online or in person)   |                        | Patients
Physicians | Patients
Physicians | Patients
Physicians |
| Complete the post-visit checklist                          |                        | Physicians             | Physicians             | Physicians             |
| Complete the online sociodemographic questionnaire         |                        | Patients
Physicians |                        |                        |
| Complete the online study questionnaire                    |                        | Patients
Physicians | Patients
Physicians | Patients
Physicians |
| Possibly participate in an online qualitative interview    |                        |                        | Patients               | Patients               |
| Participate in an online focus group                       |                        |                        | Physicians             | Physicians             |
| Receive compensation                                       |                        | Patients               | Patients               | Patients               |

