## Aim and objectives

With the present mixed method pilot study, drawing on implementation science, the aim is to develop the methods and tools necessary to undertake a more robust evaluation of the implementation and effectiveness of the I-Score ePROM-within-Opal innovation (henceforth, the I-Score intervention) in routine HIV care with individuals on ART. This study's primary objectives are to evaluate perceptions of the I-Score innovation (Objective 1) and evaluate the implementation strategy (Objective 2) in terms of recommended implementation science metrics for patient-reported outcome measure initiatives in routine care (Stover et al., 2020). Its secondary objective (Objective 3) is to determine if the intervention shows promise and the chosen outcomes are useful, by observing collected data on select effectiveness outcomes (patient and service outcomes).

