## Methods

### Study design

This 6-month pilot study will adopt a one-arm mixed method type 3 implementation-effectiveness hybrid design and be conducted in a single clinical site (see Figure 3). Type 3 hybrid designs emphasize testing the implementation strategy of an evidence-based intervention, but merely observing data collected on intervention effectiveness (Curran et al., 2012). While syntheses of effectiveness evidence for PROM use in routine care have typically found mixed results, with inconsistent impacts on patient outcomes (e.g., Boyce et al., 2013, Valderas et al., 2008), a more recent systematic review finds the evidence supports PROM use in standard care, particularly to improve patient-provider communication and decision-making in clinical practice (Isaque et al., 2019). The hybrid design also seems justified, given international momentum for PROM use (Rutherford et al., 2020), which may build with the COVID-19 pandemic. Indeed, there are calls for a scale up of electronic PROMs implementation in this crisis for the remote follow-up of chronic conditions, in part, to better screen patients and promptly manage their needs (Marandino et al., 2020).

Mixed methods were adopted in this study as multiple methods are recommended for studying intervention implementation and its problems in complex systems, like HIV clinics (Peters et al., 2013). Regarding the integration of the quantitative and qualitative data collected, this will occur toward study end within a convergent parallel design (Creswell and Plano Clark, 2011). Those directly involved in the analyses will decide upon the specifications of integration. Reporting of this study will seek to satisfy the standards of Good Reporting of a

Mixed Methods Study (O’Cathain et al., 2008) and the Standards for Reporting Implementation Studies (Pinnock et al. 2017).

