### Setting and participants

The study setting is a large hospital-based clinic in Montreal, Quebec, Canada. This clinic, the Chronic Viral Illness Service (CVIS) of the MUHC, offers multidisciplinary care to approximately 2000 adults living with HIV. Five physicians treating individuals with HIV at the CVIS will be recruited to participate as well as 30 of their adult patients. This sample size amply meets rule of thumb recommendations for one-arm pilot studies (Sim & Lewis, 2011). Patients must be confirmed HIV-positive, have a history of known or suspected adherence problems in the past year, be aged at least 18 years old, be on or beginning combination ART, be literate in English or French, and own a smartphone. Full details on eligibility are presented in the next section. Ten female patients will be recruited, to ensure sufficient representation of women living with HIV (Public Health Agency of Canada, 2018).

[figure not shown]

Figure 3. Pilot study design.

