## **Data analysis**

### **Quantitative analysis**

Time 1 questionnaires for people living with HIV and for HIV physicians will be summarized with descriptive statistics. For continuous variables, the minimum, the maximum, the mean, and the standard deviation will be reported. For ordinal and nominal qualitative variables, we will report absolute and relative frequencies (proportions).

As, specified, for most quantitative metrics relating to Objectives 1 and 2, as recommended for pilot studies, score targets were set to evaluate the ability to proceed to a definitive trial (Thabane et al., 2010). For people living with HIV and HIV physicians, continuous outcomes expressed on a Likert scale will be summarized with the minimum, the maximum, the mean, and the standard deviation at T1, T2 and T3. Binary outcomes (yes or no) will be reported with absolute and relative frequencies (proportions) at T1, T2 and T3. The means and proportions of T1, T2 and T3 will be confronted with their corresponding thresholds for success, presented in Table 2. To study the tendency of means and proportions for people living with HIV over time, a Linear Mixed Model (LMM) or a

Generalized Linear Mixed Model (GLMM) will be used, for continuous and binary outcomes, respectively. The response variable of each model will be the corresponding outcome and the independent variable will be the time (T1, T2 and T3). The null hypothesis of no time effect on the corresponding outcome will be tested with a Student's t-test on the regression coefficient. If the null hypothesis is rejected, we will perform post-hoc Student's paired t-tests between all combinations of time points to show between which time points means and proportions differed significantly. Additionally, to verify if each threshold for success is met at the end of the study, we will test the null hypothesis that each mean or proportion at T3 is inferior to its corresponding threshold with a Student's t-test. For all analyses, a significance level of 5% will be adopted. Finally, where appropriate, Cronbach's alpha will be calculated to evaluate the internal consistency of subscales.

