|                         | Ensure open channels of communication with time and space for clinicians to criticize and feedback on the PROM process | Process: Reflecting & evaluating | -                                   | Plan: Organize clinician implementation team meetings                                                                                                                                                                                                                    |
|                         | Implementation leads must consider feedback and use it to develop the process                                          | Process: Reflecting & evaluating | -                                   | Quality management: Conduct cyclical small tests of change

Building on feedback received from patients and physicians and the Application Manager's field notes, we will use a rapid-cycle evaluation approach, using the CFIR, to improve implementation. |

*Note.* PROM = patient-reported outcome measure; CFIR = Consolidated Framework for Implementation Research; \* Reproduced or adapted from Foster et al. (2018); \*\* Based on Damschroder et al. (2009); \*\*\* Based on the taxonomies of Powell et al. (2012, 2015).

Table 3. Implementation science metrics and effectiveness outcomes collected for the pilot study.

| Objective                                                                                   | Construct                 | Data collected                                                                                              | Threshold for success | Participant group |            | Timing     |
|---------------------------------------------------------------------------------------------|---------------------------|-------------------------------------------------------------------------------------------------------------|-----------------------|-------------------|------------|------------|
|                                                                                             |                           |                                                                                                             |                       | Patients          | Physicians |            |

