| Objective 3
– Determine preliminary intervention effectiveness & outcome measure utility | Patient management        | Checklist of physician actions following review of the I-Score results                                      | $p \leq 0.05$         | -                 | ✓          | T1, T2, T3 |
|                                                                                             | Barriers to ART adherence | The I-Score PROM                                                                                            | $p \leq 0.05$         | ✓                 | -          | T1, T2, T3 |
|                                                                                             | Adherence to ART          | Self-Rating Scale Item (Feldman et al., 2013)                                                               | $p \leq 0.05$         | ✓                 | -          | T1, T2, T3 |
|                                                                                             | Viral load                | The HIV RNA viral load, as indicated in the patient's medical file (> 50 copies = detectable)               | $p \leq 0.05$         | ✓                 | -          | T1, T3     |

PROM: patient-reported outcome measure; ART: antiretroviral therapy. \* Qualitative data include the Application Manager's notes (T1-T3), the qualitative interviews with patients and the focus groups with physicians (T2, T3).

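### Table 3 sets p ≤ 0.05 as the success threshold for all four Objective 3 outcomes, so the progression sentence conflicts with the protocol's own statement that readiness to proceed rests on Objectives 1 and 2

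*Protocol*

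**What the plan says.** Study metrics and instruments refers the reader to a table of metrics and thresholds, then states: "Not meeting the set thresholds for success, in this study, will signify that modifications are necessary before proceeding to a definitive trial". The text calls this Table 2, but the metrics are printed in Table 3. The sentence names no objective, outcome, participant group or visit, and does not say how several misses combine.

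In Table 3 the column "Threshold for success" has 16 entries. Four are p ≤ 0.05, one for each Objective 3 outcome: patient management (the service outcome), barriers to adherence, adherence and viral load.

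Three other places give a narrower scope:

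- Quantitative analysis: "for most quantitative metrics relating to Objectives 1 and 2, as recommended for pilot studies, score targets were set to evaluate the ability to proceed". Objective 3 is not named.
- Study design describes the hybrid type as "merely observing data collected on intervention effectiveness".
- Aim and objectives makes Objective 3 secondary, to be judged "by observing collected data on select effectiveness outcomes".

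Quantitative analysis also gives two ways of comparing results with thresholds: observed means and proportions at T1, T2 and T3, and a Student's t-test of each mean or proportion at T3.

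On size, Setting and participants says: "Five physicians treating individuals with HIV at the CVIS will be recruited to participate as well as 30 of their adult patients". The justification is a rule of thumb. No power is stated for any Objective 3 test.

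**The concern.** The pilot exists to judge readiness for a definitive trial, so its decision rule should mean one thing. As drafted, the progression sentence points to a column that includes four significance tests, while the analysis and design sections leave those tests out of the decision. Two analysts could read the same results and reach opposite conclusions, and the choice between readings could be made after the data are seen.

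If the p-values count, the decision turns on tests that the study was not sized for. One of them does not measure success at all: it asks whether the proportion of visits with physician action changes over time, so physicians who act consistently well from T1 would miss the threshold. The entries also carry no direction, so a significant worsening would meet them.

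**Working it through.** **The plan's own figures.** No power or joint pass probability is stated, so there is none to reproduce. The two statements of the primary target agree: 0.80 × 30 = 24 on the Acceptability E-scale sum, and 24 / 6 = 4 on the 5-point item scale.

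**Count of Table 3 thresholds**, split by the patient and physician ticks:

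| Objective | Rows with a threshold | Group-level criteria |
|---|---|---|
| 1 | 11 | 19 |
| 2 | 1 | 1 |
| 3 | 4 (all p ≤ 0.05) | 4 |
| Total | 16 | 24 |

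**Inputs.** From the protocol: 30 patients, 5 physicians, 5% significance, paired t-tests and McNemar between T1 and T3, and a logistic model with time as a three-level factor for the service outcome. The lower patient number, 24, is 80% of 30, the retention benchmark. Effect sizes, discordant shares and numbers of barrier visits are assumptions, because the protocol gives none. Tests are two-sided unless stated.

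**1. Barriers and adherence.** Power comes from the noncentral t distribution with n − 1 degrees of freedom and noncentrality d√n.

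| d (mean change / SD of change) | n = 24 | n = 30 |
|---|---|---|
| 0.3 | 29% | 36% |
| 0.5 | 65% | 75% |
| 0.8 | 96% | 99% |

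**2. Viral load.** Exact McNemar power is the multinomial probability of all splits (improved, worsened, unchanged) whose two-sided binomial p-value is ≤ 0.05.

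| Improving / worsening | n = 24 | n = 30 |
|---|---|---|
| 20% / 5% | 15% | 24% |
| 30% / 3% | 55% | 71% |
| 40% / 3% | 81% | 91% |

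**3. Service outcome.** Assume 10 to 20 visits per time point with a barrier of concern, treated as independent. Simulated two-degree-of-freedom likelihood-ratio test of the time factor:

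| Action rate at T1, T2, T3 | Share of studies with p ≤ 0.05 |
|---|---|
| 90%, 90%, 90% | about 4–8% |
| 98%, 98%, 98% | 1% or less |
| 100% throughout | 0% |
| 50%, 70%, 90% | about 51–76% |

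A steady, high action rate almost always misses the threshold.

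**4. The Objective 3 tests together**, multiplied as if independent (an assumption):

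- 0.5 SD on both scales with 20% / 5% on viral load: 0.65² × 0.15 = 0.06 (n = 24) to 0.754² × 0.235 = 0.13 (n = 30). This is before the service row.
- 0.8 SD, 40% / 3%, and an action rate rising from 50% to 90%: 0.963² × 0.809 × 0.51 = 0.38 to 0.988² × 0.91 × 0.76 = 0.68, with all four rows.

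So a pass is improbable at moderate effects or with a steady action rate, and possible only with large effects and a rising action rate.

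**5. Objectives 1–2 alone, observed values.** Simulated probability of meeting all 20 criteria (20,000 runs; within-person correlation 0.3 or 0.6; T3 only or all three visits; the missing-data row read as completeness of at least 90%):

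| Assumed truth | All 20 met |
|---|---|
| Exactly at the thresholds | about 0% |
| Moderately above (e.g. E-scale 25.5, SD 3.5) | 14–37% |
| Clearly above (e.g. E-scale 27, SD 3) | 68–81% |
| Far above (e.g. E-scale 28, SD 2.5) | 96–97% |

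This part of the rule does discriminate.

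**6. The T3 t-test on five physicians**, one-sided. For 4/5, SD = √(0.8 × 0.2 × 5/4) = 0.447 and SE = 0.447/√5 = 0.20. Against 80%, t = 0 and p = 0.50. Against 70%, t = 0.10/0.20 = 0.5 and p = 0.32. For 5/5 the SD is zero and t is undefined. No physician proportion can therefore pass. The same difficulty appears in 24 patients against 90%: 23/24 gives t = 1.40 and p = 0.09.

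**The case against.** The progression sentence does not say that any single miss, or every threshold, decides. Read with the analysis and objectives sections, it can be taken to mean Objectives 1 and 2 only. The stated consequence is modification, not stopping, and adaptation is the purpose of this pilot, with its cyclical tests of change and Plan-Do-Study-Act cycles. A miss may simply show what to adapt, and how criteria combine could be left to a later analysis plan.

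Most of this stands. A reader might infer that all 24 criteria bind and that the rule calls for modification almost however good the intervention is. The documents do not support that: the sentence does not say so, the analysis section points the other way, and the Objective 1–2 thresholds respond strongly to true performance. Even with the p-values included, large effects can pass.

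A reader might also infer that all physician thresholds should become descriptive. That does not follow either. The primary outcome is measured in physicians as well as patients, physician review of results is a core fidelity criterion, and provider reticence is an anticipated problem.

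What the objection does not remove is the conflict itself. Table 3 labels four p-values as thresholds for success, and the progression sentence refers to thresholds without excluding them. That is stated text, not a detail left for later.

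**Conclusion.** The point holds as an internal contradiction with a practical consequence. Counting the Objective 3 p-values contradicts the scope given in Quantitative analysis and the observational role given to effectiveness in Study design and in Aim and objectives. If they do count, good performance will often be labelled as needing change: 65–75% power per paired t-test at 0.5 SD, 15–24% for McNemar at 20% / 5%, and about 4–8% for the service test at a steady 90% action rate. These figures rest on assumed effects, 24–30 analysed patients and 10–20 barrier visits per time point. The conclusion about the service row depends least on them, since that test measures change and not level.

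The criticism does not extend to the Objective 1–2 thresholds on observed values. It does reach the T3 t-test where that is applied to proportions among five physicians, which cannot pass. The correction should be made before results are seen; it does not call the design into question.

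**What to change.** 1. In Study metrics and instruments, limit the progression sentence to the Objective 1–2 thresholds, judged on observed values. Name the Acceptability E-scale (mean ≥ 24) as the leading criterion, and say that any other missed threshold shows which component to adapt.
2. In the four Objective 3 rows of Table 3, replace p ≤ 0.05 with: estimate and 95% CI; not a progression criterion.
3. Keep the physician thresholds, but state in Quantitative analysis that five-physician proportions are compared with them as observed and not by t-test.

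This costs one reworded sentence, four table cells and one added line, with no new data or participants. The downside is that effectiveness p-values no longer count towards the decision to proceed. The planned tests can still be reported.
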